#### Cost-effectiveness analyses

Economic evaluation of the study intervention (with respect to potentially prevented hospital admissions, harms, reduced mortality, quality-adjusted life-years gained, and so forth) will be performed in collaboration with health economic analysts at the conclusion of the study.

### Safety measures for serious adverse events

Study progress, collected data, and clinical cases will be reviewed periodically by the study investigators. Frequency and causation of participant hospitalization and mortality will be reviewed at 6, 12, and 18 months because the study group of interest is at high risk for these occurrences. If significant differences are found between the intervention and control groups, or if serious adverse events develop throughout the study, an independent data safety board will be convened to review the appropriateness of continuing the study in accordance with the Australian National Health and Medical Research Council National Statement on Ethical Conduct in Human Research [35].

### Intervention personnel

#### Clinical pharmacist

The intervention will be conducted by a tertiary hospital-trained clinical pharmacist who has experience working in a hepatology unit and has received education from a hepatologist regarding symptoms, signs, and clinical significance of liver decompensation events. Ongoing continuous education relevant to hepatology and the management of liver patients will be undertaken throughout the study period and will consist of weekly meetings with hepatology consultants and advanced trainees as well as attendance at departmental case discussions, journal club meetings, and in-service education.

#### Senior clinician supervision

The intervention will be facilitated by specialist medical and nursing staff to provide clinical guidance and supervision to the intervention pharmacist. The pharmacist will work in collaboration with the senior hepatologists and the hepatology clinical nurse coordinator to identify and resolve MRPs and optimize therapy. At least one supervising hepatologist will be present in the clinic during the pharmacist’s working hours. Recommendations to modify therapy will not be communicated to the patient without prior discussion with a supervising clinician. The study protocol and patient education provided to participants have been approved by the clinical leadership.

### Data analysis

Data will be coded and stored in a password-protected database and analyzed using a statistical software package (IBM SPSS Statistics version 20.0; IBM, Armonk, NY, USA). Study endpoints experienced for each treatment group will be formally analyzed on an intention-to-treat basis [36]. Important potential confounders will be included in a secondary multivariate analysis (e.g., hospital admission, mortality). Post hoc subgroup analysis will be used to further explore outcomes according to the intensity of the intervention and completeness of relevant personalized education received by intervention participants.

The study endpoints will be presented quantitatively (proportions, statistical differences between groups) and qualitatively (description of discrepancies, MRPs, and some patient-reported medication beliefs and illness perceptions). All tests will be two-tailed, and significance will be set at α = 0.05. Continuous and normally-distributed variables will be presented as mean ± SD. Differences between groups will be analyzed using one-way analysis of variance. Non-normally distributed data will be presented as median (range), and nonparametric tests will be used to analyze differences between groups. Categorical data will be analyzed using Pearson’s chi-square test or Fisher’s exact test. Pearson’s correlation or Spearman’s rank correlation coefficient will be used to identify linear relationships between normally distributed and non-normally distributed continuous variables, respectively.

Differences in the study endpoints of interest will be examined between the intervention and control groups at baseline and at follow-up. The endpoints will be examined at baseline to test for homogeneity between groups (effectiveness of randomization) and to identify clinical variables that may influence endpoints (e.g., Model for End-Stage Liver Disease score; Child-Turcotte-Pugh classification; decompensation history, including event date, type, severity, and recurrence; hospitalization frequency; age; sex; biochemical abnormalities; and other prognostic variables). Clinically significant differences at baseline between groups will be adjusted for during the final analysis. Changes in the frequency of medication discrepancies, self-reported adherence, QoL, medication beliefs, illness perceptions, and patient knowledge at follow-up will be examined to measure the effect of the intervention on study outcomes at group and individual levels. The primary endpoint of medication discrepancies will be explored using total frequency of instances and frequency of instances per patient and per medication group. Comparison between intervention and control groups at baseline and *t*
_3_ will be made using total number of instances per group, total number of high/very high risk instances per group, mean/median number of instances per patient, and mean/median number of high/very high risk instances per patient.

Predictors of clinical outcomes will be identified using binary logistic regression to determine the OR (95% CI). A multivariable logistic regression model will be used to determine independent predictors for patient outcomes. The multivariable logistic regression model will be constructed using variables of clinical significance (severity of disease; decompensation history, including date, type, severity, and frequency of events; other prognostic variables) and statistical significance as determined by univariate analysis.

Time to first episode of decompensation and time to death (cause-specific and all-cause) will be assessed using Kaplan-Meier survival curves. The curves will be compared with the log-rank test statistic. Cox proportional hazards modeling will be used to calculate HRs, after testing the proportional hazards assumption. Patients will contribute person-time from the date of recruitment until the earliest of end of follow-up (12 months) or death (date of death to be obtained from medical records). Competing risks analysis will be performed in which we encode, as separate events, time to first readmission with a cirrhosis-related episode, death resulting from cirrhosis, or death resulting from other causes. This will be extended to multivariate analysis if there are a sufficient number of events.

It is anticipated that a proportion of participants (approximately 30%) will be lost from the study before completing follow-up assessments at *t*
_3_. Although the sample size calculation has been adjusted to accommodate for this loss, subjects who have completed only one assessment will be included in the analyses to establish baseline parameters in both treatment groups. With respect to changes from baseline, data imputation will be considered. In decompensated cirrhosis, dropouts due to death are informatively censored, and thus the responses of patients with missing data will be modeled explicitly. Subjects will be matched using baseline demographic and patient-reported outcomes, repeating this technique for both intervention arms. Imputation methods such as a hot-deck imputation and iterative regression imputation will be used. The sensitivity of the results to each of these methods will be assessed to quantify the degree of bias present.

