### Tailored intensity intervention

Intervention participants will receive education and advice tailored to their needs, receptiveness, and cognitive barriers. For example, a patient who has nonalcoholic steatohepatitis with well-controlled abdominal ascites and no other decompensation history would likely require a low-intensity intervention if he or she identified as adherent. Low-intensity intervention for this patient would consist of reiteration of important dietary modifications, monitoring of weight, and diuretic education. Conversely, a malnourished ex-alcoholic patient with a history of poorly controlled ascites, recurrent encephalopathy, and persistent hypotension will require high-intensity intervention. This would ideally involve inclusion of a carer/family member in the discussion to educate both parties on the potential precipitants and early signs of encephalopathy, self-titration of lactulose, and when to present to the emergency department. Pharmacotherapy education (including possible discussion of adherence aids), high-protein and low-sodium dietary modifications, daily weight monitoring (including when to contact the clinic if weight is changing significantly over short periods of time), and review of pharmacotherapy that may contribute to hypotension would also be conducted. Liaison with additional health providers may also be required.

After providing education and advice to intervention participants, the clinical pharmacist will use a structured data collection form to record topics that have been discussed, topics that were not discussed and reasons why, and whether a carer was present. Post hoc testing will be employed to explore study outcomes according to the intensity of the intervention received and the completeness of relevant information provided (*see* the “Data analysis” section below).

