### Power calculation and sample size determination

On the basis of a primary endpoint of a 50% reduction in medication discrepancies (3.12 ± 2.5 per patient [6] to 1.56 per patient), 41 participants will be required per treatment arm to achieve ≥80% statistical power. Median survival in decompensated cirrhosis is 2 years [37]. Therefore, a 6-month mortality rate between 10% and 15% among the study cohort is predicted. The Hepatology Outpatient Centre’s attendance failure/reschedule rate is approximately 20%. Therefore, a possible 30% loss will be accounted for, and at least 106 participants will be recruited.

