### Limitations

In this study, we will evaluate the effectiveness of a single pharmacist in one general hepatology clinic in Australia, and applicability of findings to other sites will be dependent on similarities in patient demographics and models of care. An important component of this study is the provision of an intervention that is tailored to the patient’s needs, receptiveness, and cognitive barriers. As a consequence of the “reactive” nature of the intervention, the information provided will be selective, and delivery will be staggered over the course of the study. Perceived variability in delivery may be due to lack of clinical indication (i.e., not providing information on precipitants of hepatic encephalopathy to patients who have never had encephalopathy), time restraints, patient disinterest, or “information overload.” Where possible, advice and education points will be reiterated and built upon during future contacts.

There will be heavy reliance on patients’ self-reported information, such as the details of their local pharmacy and general practitioner for the process of medication reconciliation; self-reported adherence; QoL; beliefs; and perceptions. This and other clinical information will also be dependent on honest patient responses to the survey questionnaires. Although this is acknowledged as a limitation, patient reporting remains the most important method of information gathering in clinical practice in terms of eliciting history and clinical status. Furthermore, self-reported adherence using the MMAS-8 has been shown to be equally as accurate as and less onerous than other methods of adherence measurement, including pill counts. Where necessary, supplemental information will be sought from patients’ family members or other carers to corroborate patients’ responses if the study clinicians have concerns about patient safety in accordance with good clinical practice.

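### Exploring outcomes by intensity and completeness of education received is confounded by prognosis and, for survival and hospitalization, open to immortal-time bias

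*Protocol article*

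**What the plan says.** The analysis appears twice in the protocol article. Under Tailored intensity intervention: "Post hoc testing will be employed to explore study outcomes according to the intensity of the intervention received", together with the completeness of the relevant information given. Under Data analysis, a post hoc subgroup analysis will "explore outcomes according to the intensity of the intervention and completeness of relevant personalized education received by intervention participants". The same section says "All tests will be two-tailed, and significance will be set at α = 0.05".

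The Tailored intensity intervention section bases intensity on the patient's needs, receptiveness and cognition, and gives two examples. A patient with well-controlled ascites, no other decompensation and self-reported adherence would probably need low intensity. A malnourished patient with a "history of poorly controlled ascites, recurrent encephalopathy, and persistent hypotension will require high-intensity intervention".

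Education is given at baseline and at three further contacts within 6 months (Study navigation). Two of these are placed at 4–6 and 12–14 weeks (Intervention description). The Limitations section adds that "the information provided will be selective, and delivery will be staggered over the course of the study", and gives lack of time and lack of patient interest among the reasons for gaps.

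The survival analysis counts person-time from recruitment to 12 months or death. The Data analysis section also expects about 30% to be lost before the 6-month visit (t3) and treats dropout through death as informative.

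**The concern.** The contrast lies entirely within the intervention arm, so randomisation does not protect it.

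- **Intensity.** If the pharmacist gives more to sicker or less adherent patients, high versus low intensity largely repeats a comparison of worse with better prognosis. The Data analysis section itself lists decompensation history among variables that may influence the endpoints. The Discussion reports that discrepancies were associated with poorer adherence and polypharmacy, so the primary endpoint is exposed as well.
- **Completeness.** Education that depends on later contacts can be received only by patients who are still alive and attending. If follow-up starts at recruitment, the time a patient must survive in order to become complete is credited to completeness.

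At stake is how the intervention is delivered. The abstract presents it as ready to adapt elsewhere, and a spurious dose-response could be read as advice on how much education to give and to whom. The estimated effect of the intervention against usual care is not at stake.

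**Working it through.** **1. Numbers available.** The plan powers on a "50% reduction in medication discrepancies (3.12 ± 2.5 per patient [6] to 1.56 per patient") and states that "41 participants will be required per treatment arm to achieve ≥80% statistical power". Check: 2 × (1.96 + 0.84)² × 2.5² / 1.56² = 40.3, so 41 per arm is reproduced. It continues: "a possible 30% loss will be accounted for, and at least 106 participants will be recruited". The 106 follows from 41 × 1.3 = 53.3, or 53 per arm. The intervention arm therefore has about 53 patients for record-based outcomes and 53 × 0.7 ≈ 37 with t3 data.

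**2. Intensity, with no education effect.** Inputs: 12.5% overall 6-month mortality, the midpoint of the plan's 10–15%. Assumptions: constant hazards; high-intensity patients have k times the hazard because of severity alone; a share s of patients receive high intensity. Let x be 6-month survival at low intensity. Solve s(1 − x^k) + (1 − s)(1 − x) = 0.125.

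Example with k = 2, s = 0.5: x² + x = 1.75, so x = 0.914. Twelve-month mortality is 1 − x⁴ = 30.1% at high intensity and 1 − x² = 16.4% at low intensity, a ratio of 1.84.

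| k (assumed) | Spurious 12-month mortality ratio, s = 0.3 to 0.5 |
|---|---|
| 1.5 | 1.42 to 1.43 |
| 2 | 1.81 to 1.84 |
| 3 | 2.55 to 2.64 |

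**3. Completeness, with no education effect.** Inputs: 30% lost before t3 including deaths, and 6-month mortality q of 10–15%. Assumptions: complete means reaching t3; the hazard is constant and equal in attenders and non-attenders. Those lost alive make up 0.30 − q. Twelve-month mortality is then [q + (0.30 − q) × q] / 0.30 in incomplete patients and q in complete patients.

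| q | Incomplete | Complete | Ratio |
|---|---|---|---|
| 10% | (0.10 + 0.20 × 0.10)/0.30 = 40.0% | 10.0% | 4.0 |
| 12.5% | (0.125 + 0.175 × 0.125)/0.30 = 49.0% | 12.5% | 3.9 |
| 15% | (0.15 + 0.15 × 0.15)/0.30 = 57.5% | 15.0% | 3.8 |

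The groups would hold about 53 × 0.30 = 16 and 37 patients.

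**4. A looser definition.** Let complete mean reaching the 12–14 week contact, taken as week 13, with a further proportion a not attending (assumed 5–20%). Deaths by week 13 are d = 1 − (1 − q)^0.5; deaths over the next 39 weeks are p = 1 − (1 − q)^1.5. Incomplete patients have mortality [d + a(1 − d)p] / [d + a(1 − d)].

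Example with q = 10%, a = 10%: d = 0.0513 and p = 0.1462. The result is (0.0513 + 0.0949 × 0.1462)/(0.0513 + 0.0949) = 44.6% against 14.6%, a ratio of 3.05. Over all combinations the ratio runs from 2.1 to 4.0.

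**5. Endpoints affected.** Survival and hospitalization come from medical records, so early dropouts still contribute and the completeness bias can act in full. Discrepancies, adherence, quality of life, beliefs, illness perceptions and knowledge are measured at baseline and t3. An early dropout has no observed t3 value, so for these endpoints the bias enters only through who remains or what is imputed.

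**The case against.** A reader might infer that high intensity must look harmful and completeness protective whatever the true effect. The protocol does not support that.

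- Receptiveness also drives content: Table 2 gives extra material to more educated or engaged patients, so better-placed patients may receive more too.
- The plan examines changes from baseline. If high-need patients start worse, regression to the mean and room for improvement could make high intensity look beneficial.
- A large enough true effect could outweigh the confounding.

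Nor are early dropouts incomplete by construction. Completeness is judged against what is relevant to each patient, education starts at baseline, later contacts partly repeat it, and the form records why a topic was not covered. A low-need patient could be complete early. The definitions in steps 3 and 4 of the working are illustrations, since the article gives no cut-points. The 20% clinic failure rate also includes rescheduled visits and does not directly measure missed pharmacist contacts.

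The analysis is labelled post hoc and exploratory, beside a formal intention-to-treat analysis, and the Limitations section discloses selective, staggered delivery. The article also plans multivariable models that include severity.

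All of this limits the strength of the claim but does not remove it. The multivariable models are not tied to this analysis. Adjustment for baseline severity would not remove immortal-time bias. The exploratory label does not tell a reader that the contrast is confounded.

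**Conclusion.** The point holds in a limited form. The planned contrast by intensity is confounded by prognosis. The contrast by completeness is open to immortal-time bias for survival and hospitalization, and to selection or imputation effects for the t3 survey endpoints. The results are likely, though not certain, to mislead about dose-response.

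Size and direction depend on the endpoint and on cut-points that the article does not give. With no true effect, the illustrations give 12-month mortality ratios of about 1.4 to 2.6 for intensity (assuming severity alone multiplies the hazard by 1.5 to 3) and about 2 to 4 for completeness (assuming constant hazard and the two definitions tried).

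The randomised intention-to-treat comparison is untouched. This is an inexpensive improvement to a secondary, exploratory analysis, and no threat to the primary result.

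**What to change.** 1. Report intensity and completeness received descriptively: topics covered, topics not covered and why, and contacts made.
2. To ask who benefits, classify every participant in both arms as lower or higher need from baseline variables only, for example decompensation history, Child-Turcotte-Pugh class and MMAS-8. Fix the rule before outcomes are examined. Estimate the randomised arm difference within each need group, with an arm-by-need interaction, labelled exploratory.
3. If an analysis by delivery received is kept because delivery itself is of interest, adjust for baseline severity, use a landmark or a time-dependent exposure for survival and hospitalization, and state that it is non-randomised. The need subgroup answers a different question and does not replace a description of delivery.

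**Cost.** Wording in the analysis plan and a classification from data already planned for both arms. Recruitment is complete, but no new data are needed.

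The downside is low power. Assume 37 per arm with t3 data, split evenly by need (18.5 per cell), and SD 2.5. The interaction then has standard error 2.5 × √(4/18.5) = 1.16, and 80% power needs a difference in effects of about 2.80 × 1.16 = 3.3 discrepancies. That exceeds the assumed usual-care mean of 3.12, so the interaction should be presented as an estimate with its confidence interval and a non-significant result should not be read as equal benefit.

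### Covariates are to be chosen from observed baseline imbalance, and the baseline discrepancy count is not fixed as a covariate in the primary comparison

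*Protocol article*

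**What the plan says.** All statements are in the protocol article, mostly under Data analysis.

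- **Between-arm test.** For normally distributed variables, "Differences between groups will be analyzed using one-way analysis of variance". Otherwise nonparametric tests are used. Neither carries a covariate.
- **Baseline comparison.** The endpoints are compared between arms at baseline "to test for homogeneity between groups (effectiveness of randomization"), and also to find clinical variables that may influence them. The variables listed as examples end with an unspecified group of other prognostic variables.
- **Adjustment rule.** "Clinically significant differences at baseline between groups will be adjusted for during the final analysis".
- **Status of adjustment.** "Important potential confounders will be included in a secondary multivariate analysis (e.g., hospital admission, mortality").
- **Data available.** Table 3 and the Primary outcome section have discrepancies measured at t0 and t3 in both arms.
- **Change from baseline.** Changes in discrepancy frequency and in the questionnaire scores will be examined to measure the intervention's effect. No model for change is given.

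**The concern.** In a randomised trial, baseline differences between arms arise by chance. A homogeneity test therefore cannot show which covariates belong in the model; prognostic strength can. The covariate most likely to be prognostic for the t3 discrepancy count is the t0 count. Under the stated rule it enters only if the arms happen to differ on it by an amount someone judges clinically significant.

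Two things are at stake. The first is precision: the trial collects the baseline count from everyone but would use it as a covariate only in the minority of outcomes where imbalance appears. The second is a fixed analysis. With no threshold and an open list, the form of the estimate is settled after the data are seen. One paragraph makes adjustment secondary and the next places it in the final analysis, so the reader cannot tell which estimate leads.

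**Working it through.** **Inputs from the documents.** Two-sided α = 0.05 (Data analysis). Means and SD "3.12 ± 2.5 per patient [6] to 1.56 per patient", so the difference is 1.56 and the standardised difference is 1.56/2.5 = 0.624. Size: "41 participants will be required per treatment arm to achieve ≥80% statistical power". Loss: "Therefore, a possible 30% loss will be accounted for, and at least 106 participants will be recruited".

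**Assumed.** The correlation r between the t0 and t3 counts is not given, so a range is shown. Outcomes are treated as normal. The thresholds for the imbalance rule in step 5 are also assumed, because the plan states none.

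**1. Reproduce the plan's figure.** n per arm = 2 × [2.5 × (1.960 + 0.842)/1.56]² = 40.3, rounded up to 41. This is the unadjusted two-sample formula, so the design credits nothing to the baseline count.

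**2. Completers.** 106 × 0.70 = 74.2, about 37 per arm. Unadjusted t-test power at 37 per arm is 75.4%.

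**3. Adjusting for the baseline value.** Residual variance is multiplied by (1 − r²), so the effective n per arm is 37/(1 − r²).

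| r (assumed) | Effective n per arm | Power |
|---|---|---|
| 0.3 | 40.7 | 79.4% |
| 0.4 | 44.0 | 82.5% |
| 0.5 | 49.3 | 86.6% |
| 0.6 | 57.8 | 91.4% |

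The planned 41 per arm is recovered at r = √(1 − 37/41) = 0.31.

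**4. A raw change score instead.** Variance is multiplied by (2 − 2r).
- Since 1 − r² = (1 − r)(1 + r) and 1 + r < 2, this is always larger than the ANCOVA factor when r < 1.
- It exceeds 1, and so is worse than no adjustment, when r < 0.5.
- With effective n = 37/(2 − 2r), power is 60% at r = 0.3, 75% at r = 0.5 and 84% at r = 0.6.

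**5. Adjusting only when imbalance is seen.** This was simulated with 20,000 trials per setting, 37 per arm and normal outcomes (simulation error on a 5% rate is about 0.15 percentage points).

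| Rule | Type I error at r = 0.3 / 0.5 / 0.7 | Power at r = 0.3 / 0.5 / 0.7 |
|---|---|---|
| Never adjust | 4.7 / 5.0 / 4.8% | 75 / 75 / 76% |
| Always ANCOVA | 4.9 / 4.9 / 4.9% | 78 / 86 / 96% |
| Adjust if baseline p < 0.05 | 4.6 / 4.2 / 3.5% | 75 / 76 / 78% |
| Adjust if difference > 0.3 SD | 4.4 / 3.7 / 2.6% | 76 / 78 / 82% |
| Take the smaller p-value | 6.2 / 7.3 / 7.9% | not a legitimate comparison |

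The p < 0.05 rule triggers adjustment in about 5% of trials and the 0.3 SD rule in about 20%. Both leave power close to the unadjusted figure. At r = 0.3 the fall in type I error is slight; it grows with r.

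**The case against.** **The baseline is not ignored.** Changes in discrepancy frequency are to be examined as a measure of effect, and the missing-data paragraph also refers to changes from baseline. This stands: a reader might infer that the plan discards the baseline data, and the text does not support that. But no model is given for change, and step 4 shows that a raw change score is not a substitute for adjustment.

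**Inflated type I error.** A reader might infer that the imbalance rule inflates false positives. Applied mechanically, it does the opposite. Inflation appears only if the analyst chooses the more favourable result, which the plan does not propose. The undefined threshold leaves room for it, and no more than that can be said.

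**Adjusting for post-randomisation events.** A reader might take the bracket naming hospital admission and mortality as a list of confounders, which would mean adjusting for trial outcomes. The bracket can equally name the endpoints to be analysed that way. The context supports that: the Hospitalization and mortality section interprets those outcomes in light of prognostic variables, admissions in the 2 years before recruitment are collected, and patients who have died have no t3 survey. No bias is shown, and only the wording needs clarifying.

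**Secondary versus final.** The reference to the final analysis may mean timing only, with the unadjusted result leading. That is a fair reading, but the text does not settle it.

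**Size of the gain.** It rests on an assumed r and on normal theory for a skewed count. The 3.12 ± 2.5 figure describes discrepancies generally, while the Primary outcome section also counts high and very high risk ones, to which the gain may not carry over.

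**Detail left to an analysis plan.** A list of covariates could reasonably sit there. The imbalance rule itself is written in the protocol, and a fixed model would have to override it.

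**Conclusion.** The point holds as a badly fixed analysis choice that should be changed. The protocol selects covariates from observed imbalance, without a threshold or a closed list, after testing whether randomisation worked. Its named between-arm tests are unadjusted, and the t0 count is not fixed as a covariate.

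Under a mechanical version of the rule, most of the precision gain is lost (at r = 0.5, power is 76% to 78% against 86% for routine adjustment) and the test becomes conservative. For planning purposes the gain is about 75% to between 79% and 91% at 37 completers per arm. That is illustrative, resting on assumed correlations of 0.3 to 0.6, normal outcomes and the plan's own 30% loss. The case for changing the rule does not depend on the exact figure.

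**What to change.** - **Primary model.** Pre-specify one model of the t3 value by arm with the t0 value as covariate: a count model such as negative binomial for discrepancies, and ANCOVA for the scale scores. State that this estimate leads and that any unadjusted result is supportive, which also reconciles the two paragraphs of Data analysis.
- **Covariates.** Name any further covariates in advance and limit them to values from before randomisation, for example baseline Child-Turcotte-Pugh class or admissions in the 2 years before recruitment. Build the t0 count used as covariate from sources common to both arms, because interview reconciliation is done only in the intervention arm.
- **Delete** the baseline homogeneity tests and the imbalance-driven adjustment, and present the baseline table descriptively.
- **Clarify** that the bracket on hospital admission and mortality names outcomes, or admissions before enrolment, and not covariates arising after randomisation.

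The cost is wording only, since the variables are already collected. Trial status reports recruitment as complete, so the change should be made and dated before any between-arm t3 result is seen.
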